#### Efficacy analysis (Adjustment analysis)

2.10.5

Efficacy analysis indicators will include changes in the main efficacy indicators from the initial visit (baseline) to each follow-up period.

Logistic regression analysis will be used to study the relationship between continuous dependent variables and independent variables. Influencing factors will be analyzed to determine which independent variable influences the probability of dependent variable occurrence. The decision analysis method will be used to estimate the probability of each category of the dependent variable (in the presence of a combination of various independent variables), to predict the outcome. The mixed effect of multiple covariates on treatment outcome will be adjusted using the propensity score matching method. First, we will determine if the distribution of patients with similar tendentiousness score is balanced among the groups. The distribution of patients will then be adjusted according to the tendentiousness score to calculate the effect estimation value. Stratified analysis will be conducted based on patients’ PASI score which will be divided into 4 groups based on the 4 levels of PASI score (less than 10,10–20,20–30 and more than 30).

#### Safety index analysis

2.10.6

The safety index denotes the incidence of adverse events and abnormal changes in laboratory test results.

Adverse events will be listed based on the classification of adverse reactions and unrelated adverse events. Adverse reactions will include those that are “definitely related” and “possibly related” in this study.

Chi-square test or accurate probability method will be used to compare the incidence of adverse events between the 3 groups.

Changes in laboratory test results before and after treatment will be listed. Differences before and after standardization will be evaluated based on the normal value ranges for each central laboratory, in addition to the specific situation of the enrolled patient. Normality and abnormality will be determined using the normal value range table from each central laboratory and whether it has clinical significance.

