### Study design

2.1

This is a prospective, multicenter cohort study. The study was initiated in July 2019 and will end in December 2021. We plan to recruit 1521 psoriasis vulgaris patients from 14 hospitals in Beijing, Tianjin and Hebei province. All patients will be given therapies based on TCM and Conventional therapy guidelines and then followed-up for 1 year. Prior to recruitment, each participating hospital should be required to obtain ethics approval. Each participating hospital will follow a standard set of procedures. The flow chart of the study is depicted in Figure 1.

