#### Patient cohort division

2.3.2

Patients received TCM will be classified as the TCM treatment cohort. The TCM treatment course should occupy more than half of the total course of treatment, with the following stratigies:

(1)oral herbal medicine once a day(2)external use of Chinese medicine ointment with the area of body surface area (BSA) greater than or equal to the 10% of patients’ total BSA(3)acupuncture treatment(4)external use of TCM bath.

Patients received Conventional therapy following guidelines will be classified as the Conventional therapy cohort. Conventional therapies includ: external use of drugs (Cuticle promoter and Exfoliator pledge agent, glucocorticoid, vitamin D3, vitamin A acid derivatives, immunomodulatory drugs, and so on), Internal use of drugs (antibiotics, retinoic acid, glucocorticoid and immunosuppressants, biological agents, and so on). The treatment course should occupy more than half of the total course of treatment, with the following strategies:

(1)oral use of chemical drugs(2)external use of chemical drugs ointment with the area of BSA greater than or equal to 10% of the total BSA(3)biological agents injection.

Those who meet the requirements of TCM and Conventional therapy cohort meanwhile will be classified as the integrated therapy cohort.

Study assistants will be responsible for the initial visit and follow-up of each patient. The data collection schedule is shown in Table 1.

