### Safety evaluation

2.6

Safety evaluation was performed by observing adverse events (detailed records at any moment), in addition to evaluating symptoms, abnormal laboratory findings or other examinations (physical and laboratory examinations including blood routine, liver and kidney function, and biochemical examination). Adverse events will be identified by comparison, and causal analysis of adverse events will be performed according to “positively relevant,” “very likely relevant,” “probably relevant,” “probably irrelevant,” and “positively irrelevant.”

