### Sample size calculation

2.7

The sample size of this study was calculated based on the recurrence rates which is the primary outcome. According to the previous study, taking methotrexate as an example, the recurrence rate of conventional therapies is 73.7%,^[5]^ The recurrence rate of integrated Chinese Medicine is 28.6%,^[20]^ We suppose the recurrence rate of TCM group was 20%. Using non-equality test design by the PASS software, we set the α=0.05 and the power 1-β=0.8, the ratio of cases among each group is 1:1:1, the number of cases calculated is 390 in each group. We suppose a 30% of lost in the follow-up Of the study, the ultimately needed cases in each group is 507.

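### The only stated between-cohort adverse-event comparison is an unadjusted chi-square or exact test across three treatment-defined cohorts, although efficacy is to be adjusted

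*Protocol article*

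**What the plan says.** All references are to the protocol article.

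- **Design and cohorts.** Section 2.1: "This is a prospective, multicenter cohort study". Section 2.3.2 forms the groups by treatment received: "Patients received TCM will be classified as the TCM treatment cohort", on the condition that "The TCM treatment course should occupy more than half of the total course of treatment". The conventional cohort has a parallel rule, and patients who meet both rules form the integrated cohort.
- **Safety data.** Section 2.6: "Safety evaluation was performed by observing adverse events (detailed records at any moment". Section 2.1 plans one year of follow-up for everyone. Section 2.7 adds "We suppose a 30% of lost in the follow-up Of the study", as one overall figure.
- **Safety analysis.** Section 2.10.6: "The safety index denotes the incidence of adverse events and abnormal changes in laboratory test results". The between-cohort comparison is "Chi-square test or accurate probability method will be used to compare the incidence of adverse events between the 3 groups". Section 2.10.1 makes tests two-sided, with P below .05 significant.
- **Adjustment.** Section 2.10.5, whose heading names efficacy: "The mixed effect of multiple covariates on treatment outcome will be adjusted using the propensity score matching method". It also stratifies by baseline severity. Section 2.10.2 names survival analysis and Cox regression for new skin lesions. Section 2.10.4 lists covariates for adjusted analysis without naming an endpoint.

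**The concern.** In cohorts defined by treatment received, a crude difference in the proportion with an adverse event mixes three things: the effect of treatment, the kind of patient who received it, and how long each cohort was observed. The protocol handles the second for efficacy and the third for new lesions, but its named test for adverse events handles neither.

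Both routes are plausible here. Baseline severity, psoriatic arthritis and recent medical history are on the protocol's own covariate list, and each could be related to treatment and to adverse events. With 30% loss expected, a cohort that loses more patients, or loses them earlier, has less time in which events can be recorded. If incidence is computed over all enrolled patients, that cohort looks safer.

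The Introduction motivates the study partly by the side effects of conventional therapy. A statement about relative safety is therefore a foreseeable use of this table, and a significant P-value could be read as a treatment difference when it is not one.

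**Working it through.** **The plan's own figures.** The protocol states no number for the safety comparison. Its sample size, for recurrence, reproduces: 20% versus 28.6%, two-sided alpha 0.05, power 0.80, pooled variance and no continuity correction give 390 per group, and 390 × 1.3 = 507. Only the 507 per cohort is used below.

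**Question.** How often does the planned three-group test reject when treatment has no effect on adverse events?

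**Method.** For true proportions p₁, p₂, p₃ with mean p̄, the chi-square statistic on 2 degrees of freedom has approximate noncentrality λ = 507 × Σ(pᵢ − p̄)² / [p̄(1 − p̄)]. The rejection probability is the chance that it exceeds 5.99. All event risks, loss splits and severity mixes are assumptions.

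**(a) Unequal loss only, same event hazard in every cohort.** With one-year event risk p and one-year loss d, and constant hazards, h = −ln(1 − p) and g = −ln(1 − d). The proportion with a recorded event is h/(h + g) × [1 − exp(−(h + g))].

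Worked case: p = 20%, so h = 0.2231. Loss of 15/30/45% gives g = 0.1625, 0.3567 and 0.5978. Recorded proportions are 18.5%, 16.9% and 15.2%, p̄ = 0.169 and λ = 1.96. Rejection is **22%**.

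| Loss in the three cohorts | Rejection at 20% event risk |
|---|---|
| 30/30/30% | 5% |
| 20/30/40% | 12% |
| 15/30/45% | 22% |
| 10/30/50% | 37% |

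With loss of 15/30/45%, event risks from 10% to 50% give 13% to 59%.

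**(b) Unequal case mix only.** If a share s of a cohort is at higher risk, with base risk b and risk ratio RR, the cohort risk is b(1 − s) + b × RR × s.

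| Higher-risk share | RR | Base risk | Cohort risks | λ | Rejection |
|---|---|---|---|---|---|
| 20/30/40% | 1.5 | 10% | 11.0/11.5/12.0% | 0.25 | 7% |
| 20/30/40% | 1.5 | 20% | 22/23/24% | 0.57 | 10% |
| 20/40/60% | 2 | 10% | 12/14/16% | 3.37 | 36% |
| 20/40/60% | 2 | 20% | 24/28/32% | 8.05 | 72% |

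With only the 355 per cohort who remain after 30% loss (507 × 0.7), these four become 6%, 8%, 26% and 56%.

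**(c) Would the remedy work?** 1,000 simulated studies per row with no treatment effect, 507 per cohort and 20% base event risk. Where case mix differs, higher-risk shares are 20/40/60% with hazard ratio 2. The comparison is the crude test against a Poisson model with log observation time as offset, adjusted for the risk factor.

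| Imbalance | Crude test | Adjusted person-time model |
|---|---|---|
| None (30% loss in each) | 5.7% | 5.9% |
| Loss only (15/30/45%) | 21.6% | 4.9% |
| Case mix only (30% loss in each) | 45.4% | 4.5% |
| Both, same direction | 92.9% | 4.4% |
| Both, opposite directions | 9.1% | 6.0% |

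This is a best case for the adjusted model: the risk factor is measured, and loss is unrelated to adverse events given that factor. The 45.4% is below the 72% in (b) because equal loss is included and a hazard ratio of 2 is weaker than a risk ratio of 2 (36% against 40% in the higher-risk group).

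**The case against.** The strongest reply has four parts.

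1. **Section 2.10.4 may already cover safety.** It precedes both the efficacy and the safety sections, promises adjusted analysis and names no endpoint. In a condensed article, supporting safety models may sit in an analysis plan not shown. This reading is possible. It does not settle the point, because section 2.10.6 names its own test and that test is unadjusted.
2. **Crude adverse-event tables are routine, and safety is not a listed outcome.** Both statements are true. Adverse events are absent from the main and secondary outcomes and from the Discussion's list of what patients will be evaluated on, and no planned claim that TCM is safer is stated. This lowers the importance. It does not make a significance test across treatment-defined cohorts interpretable as a treatment comparison.
3. **Unequal observation is not stated.** Follow-up is one year for all and loss is a single 30%. Section 2.10.6 does not define the denominator for incidence. The observation-time route therefore depends on loss differing between cohorts and on a simple proportion being used.
4. **Person-time models are only a partial remedy.** They assume that leaving is unrelated to adverse-event risk. This stands in full.

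Stronger readings that the document does not support:

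- A reader might infer that the protocol concedes the cohorts are not comparable. Section 2.10.4 only says that comparability will be examined.
- A reader might assume that treatment is chosen by severity, comorbidity or earlier treatment. That is reasonable for a cohort study but is not stated, and the exclusion of serious systemic disease narrows the comorbidity route.
- A reader might quote a far larger error from unequal follow-up. In a two-group test with 0.3 events per year, mean observation of 1.0 versus 0.7 years gives about 76% rejection. If loss is spread evenly over the year, that needs no loss in one cohort and about 60% in the other, which an overall 30% does not suggest.

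**Conclusion.** The point holds in limited form. As written, section 2.10.6 bases the only stated between-cohort adverse-event comparison on a test that keeps its 5% level only if loss and case mix are balanced (or happen to offset each other), and nothing in the design ensures that.

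Under the assumed imbalances the false-positive rate is about 12% to 37% from unequal loss at a 20% event risk, and about 7% to 72% from case mix. Opposing imbalances can largely cancel. The bias is possible, not demonstrated. Its direction is unknown, so the document does not support saying that the plan favours TCM. Because safety is not a listed outcome, this is worth correcting but is of secondary importance.

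**What to change.** In section 2.10.6:

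- Keep the chi-square or exact table and label it descriptive.
- State that any between-cohort safety conclusion will rest on an analysis adjusted with the baseline covariates or propensity score already planned for efficacy.
- Where event dates and last-contact dates are recorded, report adverse events per person-time in each cohort. Compare cohorts by a rate model with log observation time as offset, or by time to first event.
- Limit the models to all adverse events and the common categories.
- Report loss, and its reasons, by cohort beside the safety results.

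**Cost.** A few sentences and a small number of models. Baseline covariates are already planned. Whether event and last-contact dates are captured cannot be confirmed, because the data collection table is not shown. If they are not, the covariate adjustment can still be done, but the person-time part needs extra data fields. Intervals for rarer events will be wider. If patients leave because of adverse events, person-time models do not remove that bias, and the report should say so.

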Patient management, collection, and analysis of medical data is the aim of the present clinical study. Management of chronic diseases will be investigated using this methodology. Patients will be initially registered using unique codes and then will undergo the relevant examinations based on an standard operation process to ensure consistency. Second, patients will be regularly evaluated for their disease condition by regular follow-up visits. If patients are unable to be physically present, they will be evaluated via online or telephone follow-ups. Third, doctors and patients will have direct access via Wechat IDs managed by research assistants. For common problems, the research assistants will communicate with patients via Wechat to improve patient compliance. Fourth, the database will be regularly checked. Patient treatment plans often change, so it is necessary to review and modify information regularly. Treatments will be evaluated for efficacy and actual benefits of TCM for chronic diseases. After platform establishment, enrollment of patients based on inclusion and exclusion criteria should be strictly followed. Based on preset objectives, there will be different research plans and corresponding statistical analysis required. It will be necessary to hold regular meetings to further develop the platform, share knowledge and data so that investigators can benefit from this platform.

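### Adverse-event incidence is compared between cohorts defined by the majority treatment over the whole course, so an event followed by an early switch is counted under the later treatment

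*Protocol article*

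**What the plan says.** Section 2.10.6 of the protocol article defines the safety measure: "The safety index denotes the incidence of adverse events and abnormal changes in laboratory test results". It then names the test: "Chi-square test or accurate probability method will be used to compare the incidence of adverse events between the 3 groups".

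The groups come from section 2.3.2. For the first cohort, "The TCM treatment course should occupy more than half of the total course of treatment". The conventional cohort has the matching condition: "The treatment course should occupy more than half of the total course of treatment, with the following strategies". The third is the overlap of the two: "Those who meet the requirements of TCM and Conventional therapy cohort meanwhile will be classified as the integrated therapy cohort".

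Events are collected without restriction to a treatment period. Section 2.6 says "Safety evaluation was performed by observing adverse events (detailed records at any moment", and "causal analysis of adverse events will be performed according to" a five-level relatedness scale. The scale does not say to which treatment an event is related. The Discussion adds: "Patient treatment plans often change, so it is necessary to review and modify information regularly".

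Neither 2.6 nor 2.10.6 ties an event to the treatment in use when it began, sets an exposure window or uses time at risk.

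**The concern.** In a safety comparison, the group in which an event is counted should be the treatment the patient was on when it occurred. Here the group label is known only once it is clear which therapy filled most of the course. If an event leads a patient to stop one therapy and take the other for the remainder, the event helps to decide the label. The patient then leaves the denominator of the therapy on which the event arose, and both patient and event are added to the other group. This is a systematic error. A larger sample does not reduce it.

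The contrast between herbal and conventional treatment could be understated, overstated or, with enough switching, reversed. The Discussion says that children and pregnant and breastfeeding women are included, so a safety statement from this study may be read closely.

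**Working it through.** **1. Where a switcher is counted.** Take a patient who has an event on therapy A, stops A, and takes B for the rest of the course.

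| Pattern | Majority rule met | Event counted under |
|---|---|---|
| Early switch, B fills more than half | B only | B |
| Late switch, A fills more than half | A only | A |
| Enough overlapping use of A and B | both | integrated |
| Exactly half and half, no overlap | neither | no cohort |

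Without overlap, the shares of A and B sum to at most the whole course, so both cannot exceed one half. The integrated cohort therefore does not absorb clean sequential switchers. Only the first row misplaces the event between the two single-therapy cohorts, and A can be either therapy.

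**2. Inputs for an illustration.** The plan gives no safety figure to reproduce.

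- N = 507 starters per therapy, the group size in section 2.7 (390 × 1.3 = 507).
- Assumed: event risk a on conventional therapy and b on TCM.
- Assumed: share s of conventional starters with an event who switch early enough to become TCM patients.
- Simplification: no other movement, and the integrated cohort is left out.

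**3. Formulas.** Patients moved: m = N·a·s.

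- Reported conventional incidence = (N·a − m) / (N − m)
- Reported TCM incidence = (N·b + m) / (N + m)

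**4. Results, conventional to TCM** (Pearson chi-square on expected counts). The row s = 0 is what attribution at onset would give.

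| True risks a v b | s | m | Conventional | TCM | p |
|---|---|---|---|---|---|
| 20% v 10% | 0 | 0 | 20.0% | 10.0% | <0.001 |
| 20% v 10% | 10% | 10.1 | 18.4% | 11.8% | 0.003 |
| 20% v 10% | 25% | 25.4 | 15.8% | 14.3% | 0.50 |
| 20% v 10% | 50% | 50.7 | 11.1% | 18.2% | 0.002 |
| 20% v 20% | 10% | 10.1 | 18.4% | 21.6% | 0.20 |
| 20% v 20% | 25% | 25.4 | 15.8% | 23.8% | 0.001 |

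Worked line (20% v 10%, s = 25%): m = 507 × 0.20 × 0.25 = 25.35. Conventional: (101.4 − 25.35) / (507 − 25.35) = 76.05 / 481.65 = 15.8%. TCM: (50.7 + 25.35) / (507 + 25.35) = 76.05 / 532.35 = 14.3%.

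**5. The reverse route.** Keep 20% v 10%, but let a quarter of TCM starters with an event switch early to conventional therapy: k = 507 × 0.10 × 0.25 = 12.675. Conventional: (101.4 + 12.675) / (507 + 12.675) = 114.075 / 519.675 = 22.0%. TCM: (50.7 − 12.675) / (507 − 12.675) = 38.025 / 494.325 = 7.7%. The true 10-point difference now appears as 14.3 points.

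**6. Both routes at 25%.** Conventional: (101.4 − 25.35 + 12.675) / (507 − 25.35 + 12.675) = 88.725 / 494.325 = 17.9%. TCM: (50.7 + 25.35 − 12.675) / (507 + 25.35 − 12.675) = 63.375 / 519.675 = 12.2%. The difference is 5.8 points. With equal risks and equal switching the two routes cancel.

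**7. Do other provisions repair it?** The relatedness grading in 2.6 names no treatment, and in 2.10.6 it governs a listing, whereas the stated test is on adverse events by group. Propensity matching is set out under efficacy (2.10.5). Balancing baseline covariates would not in any case move an event back to the treatment on which it arose.

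**The case against.** The strongest reply is that this is detail for the SAP. A chi-square or exact test of incidence by cohort is a standard summary, and attribution windows and person-time rates are often left out of an article. That is fair for the window and the time at risk, whose absence alone would not be a finding. It does not answer the point, because the article itself fixes both the grouping rule and the test, and an SAP that follows the two inherits the problem.

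Other objections stand and limit the claim:

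- **Direction.** A reader might infer that events on conventional drugs are charged to TCM as a matter of course. The documents do not support that. It needs an early switch, and the opposite route exists.
- **Switching.** The Discussion's remark on changing plans explains why records are reviewed. It does not say that patients cross between TCM and conventional therapy, and a change may stay within one of them.
- **Cause of switching.** A reader might assume that intolerance is a common reason to switch. The documents do not say so.
- **Size.** A large true difference disappears only under heavy one-way switching. With 500 starters each and assumed risks of 30% v 5%, half of the 150 conventional patients with an event must switch to give 75/425 = 17.6% v 100/575 = 17.4%. With one tenth, it is 135/485 = 27.8% v 40/515 = 7.8%, and the conclusion is intact.
- **Traceability.** Regimens and events are recorded throughout, so misplaced events can be found afterwards.
- **Time at risk.** Follow-up is one year for all, so incidence over a common period is a legitimate measure apart from dropout. Patient-time by current treatment answers a somewhat different question and depends on the carry-over window.

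**Conclusion.** The concern holds in conditional form. Sections 2.3.2 and 2.10.6 together let an adverse event influence the cohort in which it is counted, and no stated provision corrects this. The result is a wrong safety contrast whenever patients with events switch early enough to change their majority therapy.

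Sign and size cannot be fixed from the documents. Under the assumed 20% v 10% risks, the reported difference ranges from 6.6 points (one tenth switching from conventional to TCM) through 1.5 points (a quarter) to a reversal of 7.1 points (half). It widens to 14.3 points if a quarter of TCM patients with events switch the other way. If such switching is rare, or balanced with similar risks, the effect is small. These figures rest on assumed risks and switch shares, no switching by patients without an event, and no movement into the integrated cohort.

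The change is worth making before analysis. Safety is not among the listed main or secondary outcomes, so the primary result is not at stake.

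**What to change.** In section 2.10.6, or in the SAP text that implements it:

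- **Main safety comparison.** Attribute each adverse event and laboratory abnormality to the treatment or treatments in use at onset (TCM only, conventional only, both), with a carry-over window stated in advance. Report rates per patient-time in each of these states.
- **Secondary display.** Keep the chi-square or exact table by cohort, labelled as grouped by majority therapy over the course.
- **Listing.** Show the events that led to stopping or switching, with the treatment at the time.
- **Sensitivity analysis.** Repeat the main comparison with a different carry-over window, because results for delayed toxicity depend on that choice.

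Fixing cohorts at enrolment would not be enough alone, since events after a later switch would then be charged to the first treatment.

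The cost is analysis wording and somewhat more programming. The abstract says that regimens are recorded at inclusion and during follow-up, and section 2.6 provides for detailed event records, so no new data collection should be needed, provided that treatment and event dates are captured.
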